### Adverse events and serious adverse events

An adverse event (AE) refers to an untoward medical occurrence that happens during the trial. A serious adverse event (SAE) refers to any incident that is life-threatening or may cause significant disability, including but not limited to SIRS, cardiocirculatory instability, stroke, organ failure, or death. All AEs and SAEs will be treated immediately, and the type of event, likely cause, place and date of occurrence, and treatment of the events will be documented. SAEs must be reported to the principal investigator within 24 h and will be discussed in data monitoring committee (DMC) meetings.

### Data collection and follow-up

Participants will be evaluated and their medical information will be collected and documented according to Fig. 2.

**Fig. 2 Fig2:**
[figure not shown]
Standard Protocol Items: Recommendations for Interventional Trials (SPIRIT) figure for the POLMA-EP trial

Upon arrival, a series of baseline information will be collected, including the patient’s demographics, cause of hospitalization, elective surgery type, medical history, anaphylactic history, and co-morbidities and concomitant medication. Physiological parameters will also be collected, including blood pressure (BP), heart rate (HR), respiratory rate (RR), core body temperature (or axillary temperature + 0.5), ASA classification level, and risk for PPCs. The patient’s cardiovascular, neurological, respiratory, endocrine, and urinary functions will be evaluated and recorded. Laboratory tests including routine blood test, blood gas analysis, and pulmonary function indicators such as vital capacity (VC), forced vital capacity (FVC), forced expiratory volume in 1 s (FEV1), and peak expiratory flow (PEF) will also be measured and documented.

On the day of surgery, anesthetic and surgical recording will also be completed. This will include anesthesia type and duration, mechanical ventilation length, surgery time, PACU stay, blood products (red blood cells/plasma/platelets/fresh frozen plasma/albumin) transfusion, fluid infusion (crystalloid solution and artificial colloids), amount of bleeding, intubation type, times of attempts, ventilation mode, positive end-expiratory pressure (PEEP), tidal volume, types and dosage of anesthetic drugs, and ICU admission and stay.

The PPC level, routine blood tests, blood biochemistry, and blood gas analysis of each patient are evaluated at days 1, 3, and 7 and before discharge. Before discharge, important examinations such as pulmonary radiography and sputum and blood cultures will be completed and recorded. For PPCs, treatments including medication (drug name and dose) and mechanical ventilation (mode, duration, and other parameters) will be documented. In cases of death, the time, cause, and relativity to surgery or anesthesia will be evaluated and recorded.

A brief summary of discharge will include discharge diagnosis, hospitalization stay, ICU admission and length, and hospitalization fee. Follow-up will be done on day 28 ± 7 after surgery. Apart from the PPC score, a self-evaluating questionnaire covering overall health, daily activity level, limitations during work, pain, energy, social activity, passive emotions, personal issues, accompanying pulmonary diseases, and overall satisfaction will be completed. Another follow-up will take place on day 84 ± 7 post surgery. The follow-up will be in the form of phone-call visits by designated allocation-blinded clinicians.

Data will be collected on paper case report forms (CRFs) by nurses or clinicians blinded to group allocation and then collected onto electronic CRFs (eCRFs) by trained assistants. The eCRF is a restricted online system that is capable of alerting information inconsistencies, missing data, and atypical errors. The database will be available for editors and peer reviewers when required.

### Data monitoring

The DMC, composed of principal investigators from each center, statisticians, and representatives from the ethics committee, will be responsible for data monitoring. Members of the DMC are independent of the sponsors. Written reports on trial progress and feedback will be submitted to the committee quarterly, and cases of unexpected scenarios and SAEs will be discussed at committee meetings.

## Statistics and data analysis

### Sample size estimations

Power Analysis and Sample Size (PASS) software (version 11.0; Number Cruncher Statistical Software (NCSS), LLC, Kaysville, UT, USA) was used for the sample size calculation. The χ^2^ test for a multiple proportions procedure was used. With an α = 0.05, a power of 90%, an effect size = 0.09, and degrees of freedom = 2, we estimated that 2584 patients would be required for our study. If the attrition rate was set at 10%, a total of 6000 patients (3000 in each group) would be required. The effect size was calculated from the assumption that the LMA would cause a reduction from 15% to 10% for the incidence of PPCs. The incidence of PPCs for patients undergoing different types of surgeries has been reported to be in the range of 1–23% [5]. Therefore, a proportion of 10% of the patients in the LMA group were expected to develop PPCs, and this was used to calculate the sample size.

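### The sample-size figures do not follow from one another: effect size, degrees of freedom, the 2584 requirement and the 6000 target cannot all belong to one calculation

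*Protocol article*

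**What the plan says.** The calculation is in the protocol article under Sample size estimations. It names a chi-square procedure for multiple proportions in PASS 11 and sets alpha at 0.05 and power at 90%. The remaining inputs and the result are "an effect size = 0.09, and degrees of freedom = 2, we estimated that 2584 patients would be required for our study". The next step is "If the attrition rate was set at 10%, a total of 6000 patients (3000 in each group) would be required". The source of the effect size is given as "the assumption that the LMA would cause a reduction from 15% to 10% for the incidence of PPCs".

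Two other places bear on it. The section on blinding, randomization and allocation concealment describes two arms, LMA and ETI, allocated 1:1. The Statistical analysis section lowers the significance level to 0.025 when two chi-square tests are done, and Primary outcomes lists two outcomes: PPC incidence and perioperative mortality.

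**The concern.** The section gives its inputs, its result and the origin of its effect size, so each link can be checked, and the links do not join. The effect size does not come from the quoted rates, the degrees of freedom do not fit two arms with a binary outcome, the requirement does not come from the printed inputs, and the enrolment target does not come from the requirement and the attrition rate.

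What is at stake is the justification for randomising about 6000 patients aged 70 or over. A reader who takes the section at face value will believe that the trial is sized to detect a 5-point fall in PPCs with 90% power. At 6000 it is sized for something smaller that the text never states, so a significant difference well below 5 points would be judged against the wrong planning value.

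**Working it through.** **Inputs.** From Sample size estimations: alpha 0.05, power 90%, w = 0.09, df = 2, PPC incidence 15% vs 10%, attrition 10%. From the randomization section: two arms, 1:1. From Statistical analysis, as a variant: alpha 0.025. A chi-square test is non-directional, so alpha is treated as two-sided.

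**Step 1: the plan's own figure.** For a chi-square test, total N = λ / w², where λ is the non-centrality that gives the required power. For alpha 0.05 and 90% power, λ = 12.654 with df = 2 and 10.507 with df = 1.

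- As printed (w = 0.09, df = 2): 12.654 / 0.0081 = 1562.2, so **1563**, against the stated 2584.
- If 0.09 is a rounded value between 0.085 and 0.095, N runs from about 1403 to 1752. Rounding does not explain the gap.
- Read the other way, 2584 patients with w = 0.09 and df = 2 give 98.9% power, not 90%.

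**Step 2: effect size.** With equal arms the mean rate is (0.15 + 0.10)/2 = 0.125, and each arm lies 0.025 from it. So w = 0.025 / √(0.125 × 0.875) = **0.0756**. Other common effect measures for these rates do not give 0.09 either: Cohen's h is 0.152, and the one-sample goodness-of-fit w is 0.140 or 0.167.

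**Step 3: degrees of freedom.** Two arms by PPC yes/no gives (2 − 1)(2 − 1) = **1**. A value of 2 would fit three arms, or two arms with a three-category outcome.

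**Step 4: attrition.**

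| Reading of 2584 | Divided by 0.9 | Multiplied by 1.1 | Attrition needed to reach 6000 |
|---|---|---|---|
| Total, as the text says | 2872 | 2843 | 1 − 2584/6000 = 56.9% |
| Per arm (5168 in total) | 5743 | 5685 | 1 − 5168/6000 = 13.9% |

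Neither reading gives 6000 at 10%. The per-arm reading is also not valid for this method, because N from λ / w² is already the total over both arms.

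**Step 5: where 2584 might come from.** Two sets of inputs come close: w = 0.07, df = 2, alpha 0.05 gives 2582.4; and w = 0.0756, df = 2, alpha 0.025 (λ = 14.753) gives about 2582. The section states neither set, and both keep the wrong degrees of freedom.

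**Step 6: what the stated assumption needs.** Two-proportion test, 15% vs 10%, 90% power, no continuity correction:

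| Two-sided alpha | Per arm | Total evaluable | Randomised (÷ 0.9) | 6000 as a multiple |
|---|---|---|---|---|
| 0.05 | 918 | 1836 | 2040 | 2.9 |
| 0.025 | 1084 | 2168 | 2409 | 2.5 |

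The chi-square formula agrees: 10.507 / 0.0756² is about 1839.

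**Step 7: what 6000 delivers.** After 10% attrition, 6000 × 0.9 = 5400, or 2700 per arm. Power for 15% vs 10% is 0.9998 at alpha 0.05 and 0.9996 at 0.025. Starting from 15%, the fall detectable with 90% power is to 12.0% (3.0 points) at 0.05 and to 11.7% (3.3 points) at 0.025.

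**The case against.** The best defence is that 2584 may be genuine software output printed beside one wrong input. Changing only 0.09 to 0.07, or only the effect size and alpha (to 0.0756 and 0.025), brings the result within two of 2584. The 6000 may then be a per-arm misreading (5743) rounded up to a convenient target. On that view there are one or two slips rather than four errors, and they err towards more patients. This is plausible, but the document cannot settle it, and both routes need inputs that contradict the text. The sponsor's PASS output would show which slip occurred; it would not make the printed section correct.

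A second defence of df = 2 is that PPCs are graded 0 to 4 in Table 3, so an outcome with three categories is conceivable. The section, however, sizes the trial on a single incidence in each arm.

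Three further points do stand and limit the finding. No power for PPC is lost. A null result would still be informative about a 5-point effect: at 2700 per arm the 95% confidence interval for a difference near these rates has a half-width of 1.96 × √[(0.15 × 0.85 + 0.10 × 0.90)/2700], about 1.8 points. And 6000 is excessive only in relation to the PPC assumption. The article gives no mortality rate; if one assumes 1%, 2% or 3% in the ETI arm, 2700 per arm at alpha 0.05 detects with 90% power only falls to about 0.3%, 0.9% or 1.7%. So 6000 cannot be called too large for the trial as a whole.

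**Conclusion.** The point holds. The printed inputs give 1563 and not 2584; the quoted rates give w = 0.0756 and not 0.09; the design has 1 degree of freedom and not 2; and 10% attrition gives 2872 and not 6000. For the stated PPC assumption, 6000 is 2.9 times the requirement at two-sided 0.05 and 2.5 times at 0.025. The difference really detectable with 90% power is 3.0 or 3.3 points instead of 5.

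These figures assume 1:1 allocation, a two-sided test without continuity correction, an ETI rate of 15%, and exactly 10% attrition. With a continuity correction the requirement at 0.05 rises only to 1914 (2127 randomised), which changes nothing. The error biases no estimate and leaves the PPC test with ample power. It must still be corrected, because the enrolment target for a primary outcome rests on a calculation that cannot be true as written.

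**What to change.** Rewrite Sample size estimations from the PASS output. Remove 0.09, df = 2 and 2584; state the comparison as two proportions, 15% vs 10% (w = 0.0756, df = 1), and name the alpha used, consistently with the 0.025 in Statistical analysis. Then choose one of two statements:

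- **Preferred: keep 6000.** State that, after 10% attrition, 2700 per arm give 90% power to detect a fall from 15% to 12.0% (alpha 0.05) or to 11.7% (alpha 0.025), and more than 99.9% power for 15% vs 10%.
- **Alternatively, give the PPC requirement:** 1836 evaluable and 2040 randomised at 0.05, or 2168 and 2409 at 0.025, with the reason for enrolling more.

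The first is preferable because mortality is also a primary outcome, the smaller numbers take no account of it, and the trial is already recruiting. If 6000 was chosen for mortality or for feasibility, the section should say so. The cost is wording only: no extra patients and no change to the design.

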### Statistical analysis

Statistical analyses will be performed by an independent statistician using SAS 9.4 software (SAS Institute Inc., Cary, NC, USA). After normality testing, the patients’ data will be presented as the mean and standard deviation (SD) if they are normally distributed; otherwise, they will be presented as the mean and interquartile range. To compare numerical data, a paired or an unpaired *t* test will be used for normally distributed data, and the Kruskal-Wallis test will be used for skewed data. The χ^2^ test and Fisher’s exact test will be used to compare proportional data. When two χ^2^ tests are performed, the *P* value is adjusted to 0.025. A *P* value < 0.05 will be considered statistically significant. If *P* < 0.05, the Nemenyi test will be used to compare the difference between two groups. A logistic regression model will be developed to detect any potential confounding factors.

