**Methods/design:**

In this multi-center, randomized, parallel clinical trial, a total of 6000 elderly patients, aged ≥ 70 years, with an American Society of Anesthesiologists classification level of 1–2 and a body mass index ≤ 35 kg/m^2^, undergoing elective surgery will be enrolled and randomized into the LMA or the ETI group. Both groups will receive usual perioperative care except for the adoption of LMA/ETI. Primary outcomes are the occurrence of PPCs and patients’ perioperative mortality rates. Ease of intubation, anesthetics consumption, treatment for PPCs, duration of surgery, anesthesia recovery time and performance, time of PPC onset, postanesthesia care unit stay, intensive care unit admission and stay, in-hospital days, re-admission rates, hospitalization cost, and patients’ satisfactory scores will be secondary outcomes. Follow-up will be conducted through phone-call visits until 12 weeks after discharge.

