### Secondary outcomes

Secondary outcomes include ease of intubation (number of intubation attempts, disturbance to the following gastric tube insertion), anesthetics consumption, treatment for PPCs, duration of surgery, anesthesia recovery time and performance, time of PPC onset, postanesthesia care unit (PACU) stay, ICU admission and stay, re-admission rate, in-hospital days, hospitalization cost, and patients’ satisfactory score.

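### Skewed numerical outcomes are to be summarised by the mean with an interquartile range but compared by a rank test, so the reported centre fits neither the spread nor the test

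*Protocol article*

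**What the plan says.** The Statistical analysis section sets one rule for all numerical data. A test on the data picks the summary: "After normality testing, the patients’ data will be presented as the mean and standard deviation (SD) if they are normally distributed". For data that fail this test, the rule gives a different measure of spread but keeps the same centre: "otherwise, they will be presented as the mean and interquartile range". The comparison follows the same split. On the normal side, "a paired or an unpaired *t* test will be used for normally distributed data". On the other side the section turns to a rank method: "the Kruskal-Wallis test will be used for skewed data". The normality test and its level are not named.

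The Secondary outcomes section lists the outcomes this rule governs. They include anesthesia recovery time, PACU stay, ICU stay and "in-hospital days, hospitalization cost". None of them has a rule of its own. The article does not mention a median anywhere. The abstract describes the design as two parallel randomized groups ("In this multi-center, randomized, parallel clinical trial").

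**The concern.** In the non-normal branch three things are put together that do not belong together: the mean as centre, the quartiles as spread, and a rank test as comparison. Both branches report the mean, so failing the normality test changes only the measure of spread and the test. For a right-skewed outcome the mean sits well above the middle of the quartiles printed next to it. The P value answers a different question from the one the two means invite.

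At stake is how the secondary numerical outcomes are read. For stays and recovery time, the summary would misstate the typical patient. For cost the fault lies on the other side: the mean is the quantity that a budget needs, but the test attached to it does not compare means.

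**Working it through.** The article gives no figure on this point to reproduce. The check is of the wording, followed by an illustration of size.

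**Inputs.** From the Sample size estimations section: 3,000 patients per arm and 10% attrition, so 3,000 × 0.90 = 2,700 evaluable per arm. Assumed, because the article gives no distributions: a log-normal shape for stay and cost with log-scale SD *s*, gamma data for the normality check, and Shapiro-Wilk at the 5% level as the normality test.

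**1. How far the mean lies from the median.** For a log-normal variable:
- mean / median = exp(*s*²/2)
- upper quartile / median = exp(0.6745 *s*)
- percentile at which the mean lies = Φ(*s*/2)

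| *s* | mean / median | upper quartile / median | percentile of the mean |
|---|---|---|---|
| 0.3 | 1.05 | 1.22 | 56th |
| 0.8 | 1.38 | 1.72 | 66th |
| 1.0 | 1.65 | 1.96 | 69th |
| 1.5 | 3.08 | 2.75 | 77th |

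The mean passes the upper quartile when *s*/2 > 0.6745, that is, when *s* exceeds about 1.35. Below that it stays inside the interquartile range but above its middle value.

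**2. How often the non-normal branch is used.** Shapiro-Wilk was applied to 300 simulated gamma samples per setting. A gamma variable with shape *k* has skewness 2/√*k*.
- n = 3,000: rejection in 47% of samples at skewness 0.1, 99% at 0.2 and 100% at 0.4.
- n = 2,700: rejection in 97% at skewness 0.2 and 100% at 0.28.

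A skewness of about 0.2 is therefore enough to send an outcome to the mean-with-quartiles and Kruskal-Wallis branch almost every time.

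**3. What the mismatch can look like.** Take two log-normal arms with equal means:
- Arm A: median 7.0, *s* = 0.8, mean 7.0 × exp(0.32) = 9.64.
- Arm B: median 7.0 × exp(−0.18) = 5.85, *s* = 1.0, mean 5.85 × exp(0.5) = 9.64.

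The Kruskal-Wallis test responds to the chance that a patient in one arm exceeds a patient in the other. Here that chance is Φ(0.18 / √(0.8² + 1.0²)) = Φ(0.141) = 0.556, not 0.5. With 3,000 per arm the test gave P < 0.05 in all 300 simulated trials. A table built to the stated rule would show two identical means beside a significant P value. This example is constructed to show that the disagreement is possible. It is not a forecast for this trial.

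**The case against.** The strongest reply is that the word mean is a slip for median, and that everything else is preference. The first half may well be true, but nothing in the article corrects it. It stands in the stated analysis rule, not in background text, so it has to be put right there. Several parts of the second half also stand.

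- **Paired t test.** A reader might infer that listing "a paired or an unpaired" t test is an error in a parallel trial. The article does not limit that sentence to comparisons between arms. The Data collection and follow-up section has routine blood tests and blood gas analysis at baseline and again on days 1, 3 and 7 and before discharge, so within-patient pairs exist. What is lacking is a statement of that use. The paired test also plays no part in the mismatch between summary and rank test.
- **Normality test.** A reader might infer that choosing the method by a normality test harms every outcome. For stays and recovery time it leads to the rank test one would choose anyway, because Kruskal-Wallis with two groups is equivalent to the Wilcoxon rank-sum test. The harm there is in the summary. For cost it leads to the wrong kind of test.
- **Mean outside its own quartiles.** A reader might infer that this will happen. It needs a log-scale SD above about 1.35, and the article gives no data on spread. At 1.4 the quartiles would differ by a factor of exp(2 × 0.6745 × 1.4), about 6.6, and the patients are elective and ASA I–II.
- **No effect size or interval.** A reader might infer that none will be reported. The article does not exclude them, and such detail is commonly left to the analysis plan, which is not shown.
- **A blanket change to median.** This would create a new mismatch for cost, where the arithmetic mean is the right quantity. The fix must differ by outcome.

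**Conclusion.** The point holds for the secondary numerical outcomes. As written, a skewed outcome gets a centre that fits neither its spread nor its test, and cost gets a test that does not compare mean cost. Under an assumed log-normal shape, the mean would be 1.05 to 1.65 times the median at log-scale SDs of 0.3 to 1.0. That stay and cost are skewed is itself an assumption, but at this sample size very little skew is enough to trigger the rule.

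It would go too far to infer that the trial's main conclusion is at risk. Both primary outcomes, PPC incidence and perioperative mortality, are proportions and do not pass through this rule. This is a minor fault, worth correcting because the remedy is so cheap.

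**What to change.** Replace the single rule in the Statistical analysis section with an assignment by outcome, made in advance and not by the phrase "After normality testing":

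- **PACU stay, ICU stay, in-hospital days and anesthesia recovery time:** median with interquartile range, compared by the Wilcoxon rank-sum test (Kruskal-Wallis with two groups may stay, as it is equivalent).
- **Hospitalization cost:** arithmetic mean per arm, and the difference in means with a bootstrap 95% CI.
- **Paired t test:** state that it is only for within-patient comparisons, such as baseline against a postoperative day.

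The Trial status section says that recruitment is under way, so this can be settled before the analysis. It needs changes of wording and a little analysis work for the bootstrap interval. No new data, patients or procedures are needed.

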**Fig. 1 Fig1:**
[figure not shown]
Study flow diagram

We plan to recruit more than 6000 patients from 17 clinical centers in China. The participating clinical centers are listed in Table 1.

**Table 1 Tab1:** POLMA-EP research clinical centers

Site ID	Site name
1	Ren Ji Hospital (East), affiliated to Shanghai Jiao Tong University School of Medicine
2	Fudan University Shanghai Cancer Center
3	Shanghai Changzheng Hospital
4	Shanghai First Maternity and Infant Hospital
5	Huadong Hospital, Fudan University
6	West China Hospital, Sichuan University
7	Shanghai Guanghua Hospital of Integrated Traditional Chinese and Western Medicine
8	Shanghai Jiading District Central Hospital
9	Shanghai Pudong District Central Hospital
10	Shanghai Huangpu District Central Hospital
11	Shanghai Fengxian District Central Hospital
12	Ren Ji Hospital (West), affiliated to Shanghai Jiao Tong University School of Medicine
13	People’s Hospital of Pudong New District, Shanghai
14	Ren Ji Hospital (South), affiliated to Shanghai Jiao Tong University School of Medicine
15	First Affiliated Hospital of Wenzhou Medical University, Zhejiang Province
16	The Second People’s Hospital of Wuxi, Jiangsu Province
17	First Affiliated Hospital of Xiamen University, School of Medicine

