### Blinding, randomization, and allocation concealment

Given the nature of the intervention, blinding of caregivers or patients is not possible. However, investigators responsible for data collection and statisticians will be blinded to the study arms.

Random numbers and group allocations are generated with a 1:1 ratio and stratified according to PPC risk scores (listed in Table 2) by a central randomization system known as an interactive web response system (IWRS) developed by Beijing Blue Balloons Technology Company Limited (http://www.blueballon.cn). Allocations generated by the IWRS will be stored in opaque and numbered envelopes. Participants will be given a randomization number by the designated anesthesiologist and will be allocated according to indications inside that numbered envelope. If participants decide to withdraw after assignment, their clinical information will not be used in this trial, but their assigned random number will still be retained.

**Table 2 Tab2:** PPC risk index

Independent risk factors	Risk score
Age > 70 years	1
Cough and sputum production	1
Diabetes	1
Smoker (or patient quit within the past 6 months)	1
COPD	1
BMI > 27 kg/m^2^	1
FEV1 < 80% and FEV1/FVC < 70%	2

*COPD* chronic obstructive pulmonary disease, *BMI* body mass index, *FEV1* forced expiratory volume in 1 s, *FVC* forced vital capacity

In emergent cases when the LMA or the ETI tube cannot be placed successfully after multiple attempts, anesthesiologists may change the ventilation method or administer different treatments according to their best clinical judgement, and the patient will be excluded from the trial.

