### Intervention

Apart from the trial airway management method (LMA or ETI), other clinical decisions will be made by the practitioners at each site according to their clinical judgement and hospital protocol, including anesthesia induction, maintenance and recording, anesthetic drug use and dosage, surgical approach, and ICU treatment.

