### Primary outcomes

The primary outcomes are the incidence of PPCs (diagnostic criteria shown in Tables 3 and 4) and perioperative mortality rate.

**Table 3 Tab3:** Classifications of PPCs

Grading	Definition
0	No pulmonary complications
1	Any one of the following: cough, minor lung atelectasis (no obvious cause), dyspnea (no obvious cause)
2	Cough and sputum production (no obvious cause), bronchospasm (new-onset asthma or exacerbation of existing asthma that requires treatment), hypoxemia (SpO2 < 90% or PaO2 < 60 mmHg while breathing air), atelectasis (diagnosed by radiography or abnormal pulmonary sign with T > 37.5), hypercapnia (temporary or requires treatment; caused by medication or over-ventilation)
3	Pleural effusion (that requires drainage), suspected pneumonia (indicated by radiography, with or without microbiologic findings), diagnosed pneumonia (diagnosed based on the combination of radiology finding and microbiology evidence such as Gram staining or culture), pneumothorax (suggested by X-ray: observation of a lucent gas space devoid of pulmonary vessels between visceral pleura and the parietal pleura or symptoms of dyspnea, chest pain, irritating cough), noninvasive or invasive mechanical ventilation < 48 h
4	Respiratory failure (that requires noninvasive or invasive mechanical ventilation for > 48 h)

*PaO2* partial pressure of oxygen, *SpO2* blood oxygen saturation, *T* body temperature

**Table 4 Tab4:** Definition of PPCs

Complications	Diagnostic criteria
Pneumonia	X-ray finding of a new or progressive pulmonary infiltration and meeting 2 of the following 3 indications:
	(1) Cough, exacerbation of dyspnea or purulent sputum
	(2) Body temperature above 38 °C or under 36 °C
	(3) WBC > 12,000 or < 4000/μL
Atelectasis	Mainly based on X-ray findings as follows:
	Lung collapse
	Compensatory hyperinflation of adjacent ipsilateral lung tissue
	Wedge- or linear-shaped opacities
	Shifting of mediastinum
	Diaphragm move towards the collapse
Pleural effusion	X-ray finding of obscure or disappearance of costophrenic angle, obscured ipsilateral diaphragm
SIRS	(1) Core body temperature > 38 °C or < 36 °C
	(2) HR > 90 bpm, in cases of atrial arrhythmia, ventricular rate > 90 bpm; exclude when used medications that may affect heart rate
	(3) RR > 20 bpm, or PaCO2 < 32 mmHg (4.2 kPa), or urgent mechanical ventilation used
	(4) WBC > 12,000 or < 4000/μL

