There are several noteworthy limitations of this study. Firstly, all participating centers are located in east China; therefore, one may not postulate that results from this study can be implemented directly to other places or populations. Secondly, the long-term follow-up results are mainly based on patients’ self-evaluated questionnaires, which potentially can add bias to the results of this study. Thirdly, we are unable to apply uniform treatment to all patients. The ventilation mode adopted during anesthesia, administration of analgesics, and the prophylactic use of antibiotics, anticholinergics, and steroids are decided according to clinicians’ best judgement and will be recorded for future subgroup analysis. Other potential confounding factors [20], including surgery type and duration, will also be evaluated during statistical analysis. Moreover, the LMA device has many different forms and configurations. In this study, it is unreasonable to designate a single type of LMA device, but the mode of LMA used will be recorded. Lastly, the patient is not blinded in this trial, because extubation criteria need to be met before the LMA or the ETI tube can be removed. Even though we will make sure that every participant is informed not to reveal his/her group allocation to assessors, there is still the risk of assessor unblinding. In such cases, the patient will be evaluated by another assessor.

With our multi-center, randomized, controlled study, we aim to evaluate the safety profile of LMA/ETI use and add to the knowledge pool of airway management in elderly patients. The findings from this study can be used to help with clinicians’ understanding of the issue and can be used in clinical settings when decisions need to be made.

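### Randomisation is stratified by PPC risk score, but the only test named for the primary proportions is unstratified, which makes it mildly conservative

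*Protocol article*

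**What the plan says.** - **Allocation** (Blinding, randomization, and allocation concealment): "Random numbers and group allocations are generated with a 1:1 ratio and stratified according to PPC risk scores". The score is that of Table 2, whose items are presented as independent risk factors for PPCs. No other stratification factor is named.
- **Centres** (Study settings): "We plan to recruit more than 6000 patients from 17 clinical centers in China".
- **Primary outcomes**: "The primary outcomes are the incidence of PPCs", together with perioperative mortality. Both are proportions.
- **Test** (Statistical analysis): a chi-square test and Fisher's "exact test will be used to compare proportional data". The sample size section also rests on an unstratified chi-square test.
- **Model** (Statistical analysis): "A logistic regression model will be developed to detect any potential confounding factors". The Discussion adds that other potential confounders, "including surgery type and duration, will also be evaluated during statistical analysis". The randomisation stratum is not listed in either place.
- **Site practice** (Intervention): "other clinical decisions will be made by the practitioners at each site according to their clinical judgement and hospital protocol".

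**The concern.** Stratified allocation balances the PPC risk score between the arms, so differences in risk between strata contribute almost nothing to the chance difference between arms. A crude chi-square test does not use this. Its variance term still counts the between-stratum variation as random error. If the score predicts PPCs, as the article presumes by stratifying on it, the crude standard error is larger than the true one. The p-value is then too large, and any interval built on the same variance is too wide.

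At stake is some precision that the design has already secured. There is also a smaller matter of clarity: with a crude test beside an adjusted model whose role is not fixed, it is open which result is to be read as primary.

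**Working it through.** **Inputs.** From the article: PPC rates of 15% and 10% (pooled 12.5%), totals of 2584 and 6000, and 10% attrition, so 6000 × 0.9 = 5400 evaluable. The article does not say how the score is grouped into strata, nor what share of patients or what PPC risk each stratum has. These are assumptions below. The article gives no figure of its own for this point. (Its 2584 does not follow from its stated inputs either, but that is a separate matter. It serves here only as the smaller of two sample sizes.)

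**Formulas.** For stratum shares w and risks p, with mean risk m = Σwp:
- total variance, used by the crude test: T = m(1 − m)
- within-stratum variance, which applies after stratified allocation: W = Σ w p(1 − p)
- factor by which the crude SE is too large: √(T/W)
- actual type I error: 2[1 − Φ(1.96 √(T/W))]
- share of the sample lost: 1 − W/T

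**One case in full.** Shares 0.5/0.3/0.2, risks 7/15/35%:
- m = 0.035 + 0.045 + 0.070 = 0.150
- T = 0.15 × 0.85 = 0.1275
- W = 0.5 × 0.0651 + 0.3 × 0.1275 + 0.2 × 0.2275 = 0.1163
- W/T = 0.912 and √(T/W) = 1.047
- type I error = 4.0%; share lost = 8.8%, about 474 of 5400

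**Three assumed strata.** The first three rows use mean risk 12.5% and a constant odds ratio (OR) per stratum step.

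| Shares | Risks | Crude SE too large by | Type I error | Share of sample |
|---|---|---|---|---|
| 50/35/15% | 9.6/13.7/19.3% (OR 1.5) | 0.5% | 4.9% | 1.1% |
| 50/35/15% | 7.6/14.2/24.8% (OR 2) | 1.7% | 4.6% | 3.3% |
| 50/35/15% | 5.2/14.1/33.0% (OR 3) | 4.4% | 4.1% | 8.3% |
| 40/40/20% | 8/15/30% | 2.6% | 4.4% | 5.0% |
| 50/30/20% | 7/15/35% | 4.7% | 4.0% | 8.8% |

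With six score levels instead of three (shares 30/30/20/10/6/4%), the excess is 0.6%, 2.3% and 7.8% for OR 1.25, 1.5 and 2 per level.

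**Simulation check.** 4000 trials of 2584 patients were simulated, balanced within three risk strata. The Monte Carlo error of a 5% rate is √(0.05 × 0.95/4000) = 0.34 points.
- Type I error for OR 1.5/2/3, crude chi-square: 5.2/4.5/3.9%.
- The same, risk-stratified Cochran-Mantel-Haenszel: 5.3/5.0/5.0%.

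The stratified test holds its level. The crude test drifts low as the score becomes more prognostic. At OR 1.5 the two cannot be told apart.

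**Power for 15% versus 10%.** The crude test has 97.0% at 2584 and more than 99.9% at 5400. In the simulation at 2584 the crude test reached 97.1% to 97.9% and the risk-stratified test 97.2% to 98.2%, a gain of about 0 to 0.4 points. For a smaller effect (15% versus 12%, 5400 patients, OR 2, assumed centre SD 0.5 on the logit scale), power was 89.7% crude, 90.3% risk-stratified and 90.6% stratified by risk and centre.

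**Mortality.** The article gives no death rate. With assumed risks of 0.2/0.5/1.25% and shares 40/40/20%, m = 0.53%, 1 − W/T = 0.3%, and the crude SE is about 0.1% too large.

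**The case against.** **This may belong to the SAP.** The article lists tests by type of data, does not label one as the primary model, and does plan a logistic regression. Covariates are often settled in an analysis plan that is not shown. This stands in part: an unseen SAP may already specify a stratified analysis. But the article does name the test for proportions, and that test does not match the allocation it describes. The regression is given a different purpose.

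**The effect is small and in the safe direction.** This stands. There is no bias and no inflation of false positives, and power for the planned difference is already high. There are also reasons to expect a modest gradient: the age item applies to nearly every patient in a trial that enrols from age 70, and entry is limited to ASA I–II.

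**Stronger readings a reader might infer:**
- *That ignoring centre also makes the standard error too large.* The article names only the PPC risk score as a stratification factor. Without balance by centre, the crude test is not conservative on that account, and adjustment would only gain precision. Site discretion over care does not change this.
- *That several hundred patients are wasted.* Figures such as 474 of 5400 come from assumed four- to five-fold risk gradients. With OR 1.5 per step the equivalent is about 57 of 5400 (1.1%).
- *That the planned confidence intervals are too wide.* The article does not mention intervals, so this holds only for intervals that would be built on the crude variance.

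**Conclusion.** The mismatch between stratified allocation and an unstratified test is real, and its direction is certain if the score predicts PPCs. Its size is minor: with three assumed strata, a standard error about 0.5% to 5% too large, type I error of about 4.9% to 4.0%, and a loss of about 1% to 9% of the sample. More strata with a steep gradient would give more (7.8% in the most extreme six-level case above). All these figures rest on assumed strata and risks, since the documents give none. The conclusions of the trial are not threatened. The point is worth acting on because the correction is nearly free.

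**What to change.** State that the primary PPC comparison is a Cochran-Mantel-Haenszel test with a Mantel-Haenszel risk difference and 95% CI, stratified by the PPC risk stratum used at randomisation. A logistic model with arm and risk stratum, reported as a standardised risk difference, would serve equally. Name one of the two in advance.

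- Centre may be added as an optional precision covariate, with small centres pooled or as random intercepts.
- Keep the crude chi-square as a sensitivity analysis.
- For mortality, stratify by risk stratum only if the event counts allow.
- State how Table 2 scores are grouped into strata.

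The cost is a few sentences in the analysis plan and a few lines of SAS. The strata are already held by the randomisation system and PPC risk is recorded at baseline. The article reports that recruitment is under way, so the change can be made before the data are analysed.
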